#### Schematic of Study Design

[figure not shown]

[figure not shown]

**Primary outcomes:** Number of chronic medications, percent of individuals with one or more PIMs

**Secondary outcomes:** Adverse drug events (including falls, bleeding episodes, hypoglycemic episodes), reduction in dosage for selected PIMs (including benzodiazepines, opioids, antipsychotics), hospital, skilled nursing facility, & ED utilization, activities of daily living

## **Intervention Elements**

### **Initial Intervention**

#### **Patient / care partner intervention**

- Research analytic staff: Randomize 18 primary care clinics in Denver-Boulder service delivery area to intervention and control using block randomization scheme based on clinic size and number of potentially eligible patients. At least once a week, identify eligible patient population from intervention clinics with ADRD and MCI who have a scheduled appointment 7 or more days in advance.
- Research assistant: Enter identifiers for patients into a tracking database. Individuals with scheduled appointments will receive the following materials:
  - A cover letter providing brief information about the study along with contact information for the principal investigators and project managers. The informational letter will indicate that patients may wish to discuss medication discontinuation with their physician but are under no obligation to do so.
  - A single page tri-fold brochure with educational information on optimizing medicines through considering appropriate medication withdrawal. The brochure includes space for patients/ care partners to list questions should they wish to discuss them with their PCP at their upcoming appointment.
  - The 9-question revised Patients' Attitudes Towards Deprescribing (rPATD) questionnaire, and question about who filled out the questionnaire, along with a stamped and addressed envelope to return questionnaire.
  - Patients will receive a second mailing if they have a second appointment during the intervention period (allowing for a gap of 2 months between appointments).

- At the time of the potential second mailing, a second rPATD will be sent to patients who have not returned the rPATD from the initial mailing.

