### Study Timeline

|                                | Year 1
2019  |                 | Year 2
2019-2020 |                 |                 |                 | Year 3
2020-2021 |                 |                 |                 | Year 4
2021-2022 |                 |                 |                 |
|--------------------------------|-----------------|-----------------|---------------------|-----------------|-----------------|-----------------|---------------------|-----------------|-----------------|-----------------|---------------------|-----------------|-----------------|-----------------|
|                                | Mar
-
May | Jun
-
Aug | Sep
-
Nov     | Dec
-
Feb | Mar
-
May | Jun
-
Aug | Sep
-
Nov     | Dec
-
Feb | Mar
-
May | Jun
-
Aug | Sep
-
Nov     | Dec
-
Feb | Mar
-
May | Jun
-
Aug |
| Randomize Clinics              | X               |                 |                     |                 |                 |                 |                     |                 |                 |                 |                     |                 |                 |                 |
| Identify Eligible Participants | X               |                 |                     |                 |                 |                 |                     |                 |                 |                 |                     |                 |                 |                 |
| Initial Intervention           | X               | X               | X                   | X               |                 |                 |                     |                 |                 |                 |                     |                 |                 |                 |
| Delayed                        |                 |                 |                     |                 |                 |                 |                     |                 |                 | X               | X                   | X               |                 |                 |

|                  |  |  |   |   |   |   |   |   |  |  |  |  |  |  |
|------------------|--|--|---|---|---|---|---|---|--|--|--|--|--|--|
| Intervention     |  |  |   |   |   |   |   |   |  |  |  |  |  |  |
| 6-Month Outcome  |  |  | X | X | X | X |   |   |  |  |  |  |  |  |
| 12-Month Outcome |  |  |   |   | X | X | X | X |  |  |  |  |  |  |

304

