## 2.2 Study Enrollment Procedures

**Intervention recruitment plan.** Using EHR data and the KPCO Virtual Data Warehouse (VDW), a quality-controlled common data model derived from multiple KPCO data sources (EHR, membership, pharmacy, laboratory, and other clinical data), study personnel will identify eligible patients who receive primary care at the intervention and control clinics. At least weekly during the intervention period, study personnel will review the list of eligible participants to identify those at an intervention clinic with an appointment with their PCP 7 or more days in advance. Those with upcoming appointments will receive study materials and will be entered into a study database for tracking. Patients will be eligible to receive up to 2 mailings at least 8 weeks apart.

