#### Clinician intervention

- At the start of the intervention period, the principal investigators and the Project Manager will present a 15-minute educational session to internal medicine and family medicine PCPs at their monthly team meeting at each of the intervention clinics. The presentation will include:
  - A short slide presentation on how deprescribing is one element of optimal medication management for older adults. The presentation will include evidence-based information on what deprescribing is and when and how to consider it. It will also include example situations where deprescribing may be beneficial. The presentation will also provide general information on the study and will include contact information for the study principal investigators and local study staff.
  - We will ask clinicians to complete (on paper) at the meeting a 9-question Prescribers' Perceptions of Medication Discontinuation (PPMD) questionnaire regarding opinions on deprescribing at beginning of presentation.
  - A list of Internal Medicine and Family Medicine clinicians at each of the intervention clinics will be obtained and any providers who missed the initial presentation will be sent a letter of introduction to the study, copy of the Optimize presentation and the PPMD questionnaire, requesting that they complete it and send back to the KPCO Project Manager.
  - Newly hired physicians joining practices will be oriented to the intervention by the KPCO PI and project manager after they complete their initial clinical orientation.
- One-page paper Tip Sheets handed out to providers at monthly meetings. The Tip Sheets contain information on approaches and language to use in specific medication discontinuation situations. Eleven Tip Sheets were developed based on clinician interviews. Example topics include:
  - Limited life expectancy.
  - Potential for harm.
  - Limited evidence for effectiveness.
  - Medications have reached maximum benefit.
- Primary care clinicians will receive notification via an appointment note in the EHR when study materials have been sent to patients with an upcoming appointment.
- At the intervention conclusion, primary care clinicians will be provided a poster that is a colorful

summary of the titles of all Tip Sheets.

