## 4 STUDY PROCEDURES

### 4.1 Schedule of Evaluations for initial intervention

| Assessment                                                                     | Identify Eligible Population | Baseline, Enrollment, 2 weeks prior to scheduled visit | 6 months post brochure mailing | 12 months post brochure mailing |
|--------------------------------------------------------------------------------|------------------------------|--------------------------------------------------------|--------------------------------|---------------------------------|
| Inclusion/Exclusion Criteria                                                   | X                            |                                                        |                                |                                 |
| Demographics- age, gender, race, ethnicity                                     | X                            |                                                        |                                |                                 |
| Primary outcomes (Aim 1)                                                       |                              |                                                        |                                |                                 |
| Current Medications                                                            | X                            | X                                                      |                                |                                 |
| Number of Drugs                                                                | X                            | X                                                      | X                              | X                               |
| Percent of individuals with one or more Potentially Inappropriate Medications* | X                            | X                                                      | X                              | X                               |
| Secondary outcomes (Aim 2)                                                     |                              |                                                        |                                |                                 |
| Dose Reductions                                                                |                              |                                                        |                                | X                               |

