### 490 Definitions

of assessment variables from Schedule 4.1 above and associated data elements and sources are itemized

below. Unless otherwise mentioned, all data will be extracted from the KPCO Virtual Data Warehouse, a quality controlled, common data model that includes data from multiple KPCO data sources covering the following domains: Enrollment, utilization, pharmacy, tumor registry, demographics, lab results, mortality, vital signs, census data, geocoded demographic data, patient reported outcomes collected in the course of care, problem list diagnoses, and social history.

Inclusion/ exclusion criteria: as previously described. Data elements will include age, diagnosis codes, location of primary care provider, current medications. Chronic diagnoses will be from a list of 86 chronic conditions itemized in the Multiple Chronic Conditions Chartbook (Gerteis J, et al.). We have developed a method of counting chronic medications that utilizes the Generic Product Index (GPI) in a manner similar to prior work using the WHO Anatomic Therapeutic Chemical index A. Study experts ([name], [name], [name], [name], [name]) created a consensus-based list of GPI categories to be included in estimating the criterion of 5 or more chronic medications (this list excludes drug classes unlikely to be used as chronic medications, such as vaccines and anesthetics).

Demographics: age, gender, self-reported race/ethnicity from the EHR, census-based socioeconomic status.

Diagnoses: ICD-9 (historical) and ICD-10 codes will be used to identify diagnoses from visit billing codes, hospital and emergency department claims, and problem list diagnoses.

Current chronic medications: Total number of chronic medications on the date of study eligibility. Chronic medication use is defined as any medication for which the patient had at least a 28-day supply on the baseline eligibility date. We selected a 28-day supply (rather than a supply for a longer time period) because opioid medications are often dispensed in 28-day supplies. All current medications exclude the following domains identified by 2-digit GPI codes: Vaccines, Toxoids, Allergenic extracts, Oxytocics, Local anesthetics – parenteral, General anesthetics, Antiseptics and disinfectants, Antidotes, Diagnostic products, Chemicals, and Medical devices.

Primary Outcomes:

Number of drugs: number of chronic medications – see above.

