### **7.2 Sample Size and Randomization**

#### **Sample Size and Randomization**

There will be 9 intervention clinics and 9 control (delayed intervention clinics). We estimated power using members who would be eligible for the intervention in November 2018. Feasibility data for that cohort showed a median of 5 visits in the prior year with 99% having at least one visit and 80% scheduling a visit at least 7 days in advance. Patient materials are sent in advance of visits only for appointments made at

least 7 days before a visit, therefore, we anticipate approximately 80% of the eligible intervention population will receive mailings during the study period.

We identified 3,671 eligible members with numbers per clinic ranging from 60 to 350. For analyses of counts of medications, we will have > 80% power to detect a decrease of -0.70 (i.e. < 1 medication; power from difference in two Poisson rates in cluster-randomized trial given event rate of 6.8 and intraclass correlation coefficient (ICC)=0.01). We will be examining selected subgroups of interest, for example cohort members receiving a higher dose of the intervention or a restricted cohort with more severe dementia. Both of these comparisons could reasonably retain ~70% of the intervention cohort to contrast to the control cohort and we would be able to detect a decrease of 1.4 medications even if ICC was doubled (i.e. 0.02). Comparisons of proportions of members on a PIM will be able to detect a decrease to 29.0% or less for the intervention clinics compared to the expected rate of 35.8% for the control clinics.

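### The protocol contradicts itself on when eligibility is set: one list at the start, or a rolling baseline that tests the medication count after one arm's clinicians have been educated

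*Protocol*

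**What the plan says.** Three places read as a single list.

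- Section 2, Study Timeline: the row "Identify Eligible Participants" has one mark, in March to May 2019. This is the same column as clinic randomisation and the first quarter of the intervention.
- Section 2.2: "At least weekly during the intervention period, study personnel will review the list of eligible participants to identify those at an intervention clinic" with a PCP appointment ahead. This presupposes a list that already exists.
- Section 4.1: "Inclusion/Exclusion Criteria" is marked only where the eligible population is identified, and not in the separate baseline and enrolment column.

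Four places point to a rolling assessment.

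- Section 3.1, patient component, directly after the randomisation step: "At least once a week, identify eligible patient population from intervention clinics with ADRD and MCI who have a scheduled appointment" booked at least seven days ahead.
- Section 2.1 tests the five-medication criterion on an eligibility date that it does not define, and applies the long-term-care and hospice exclusions at baseline.
- Section 4.2 defines the count as "Total number of chronic medications on the date of study eligibility", and in the next sentence treats that date and baseline as the same.
- Section 4.2, time definitions: baseline is the time when the upcoming visit is identified and materials are mailed (intervention clinics), or the first PCP appointment in the initial intervention period (control clinics). Controls are to be screened by identical methods.

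On the clinician component, section 3.1 says: "At the start of the intervention period, the principal investigators and the Project Manager will present a 15-minute educational session". Tip Sheets follow monthly for 12 months (section 2).

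**The concern.** Five or more chronic medications is an entry criterion, and the number of chronic medications is a primary outcome. If the criterion is checked at a rolling baseline, it can be checked up to 12 months after intervention PCPs were first taught about deprescribing.

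Section 7.2 shows how selection could arise. Eligible members had a median of 5 visits in the prior year and 99% had at least one, but only 80% booked a visit seven or more days ahead. Unmailed visits to an educated PCP before baseline are therefore foreseeable. A patient reduced from 5 to 4 drugs at such a visit would fail the criterion and never enter the cohort, while the control counterpart would stay. In a trial randomised by clinic, cohort membership should rest on information that precedes the intervention.

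**Working it through.** **Step 1: which date governs entry?**

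| Item | Single-list text | Rolling text |
|---|---|---|
| Identification | Timeline: once. 2.2: list reviewed weekly | 3.1: eligible population identified weekly |
| Five-medication test | 4.1: at identification only | 4.2: on a date equated with baseline |
| Exclusions | 4.1: at identification only | 2.1: at baseline |
| Number of drugs | 4.1: recorded at identification | 4.1: recorded again at baseline |

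No section gives a calendar date for eligibility or for attributing a patient to a clinic. Even the single timeline mark shares its quarter with randomisation and the start of the intervention, so it does not show that identification comes before education.

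**Step 2: the protocol's own power figure.** Section 7.2 gives more than 80% power for a decrease of 0.70 from 6.8, with 3,671 members, 9 against 9 clinics and ICC 0.01. I assume two-sided 5% and equal clusters.

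- Mean cluster size m = 3,671/18 = 203.9; design effect = 1 + (203.9 − 1) × 0.01 = 3.03.
- SE = √[(6.8 + 6.1)/1,835.5 × 3.03] = 0.146; 0.70/0.146 = 4.8; power about 99.8%.
- Allowing for unequal clusters, a t reference with 16 df and 80% of members gives values down to 98.6%.

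The stated bound is met. Nothing below depends on it.

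**Step 3: how much could the rolling reading hide?** This is an illustration. Two inputs are assumptions: counts among eligible patients follow a Poisson truncated at 5 with mean 6.8 (the planning rate in 7.2), and a mean of 0.10 to 0.20 drugs per patient is stopped before the check, in educated clinics only.

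A truncated mean of 6.8 requires λ = 5.44, which gives P(exactly 5) = 0.272. The intervention arm has about 3,671/2 ≈ 1,836 members.

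Model A: a fraction f of patients loses one drug, whatever their count.

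- Share removed = 0.272f.
- Mean among those remaining = (6.8 − f − 4 × 0.272f)/(1 − 0.272f).
- f = 0.10: (6.7 − 0.1088)/0.9728 = 6.776.
- f = 0.20: (6.6 − 0.2176)/0.9456 = 6.750.

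Model B: each drug is stopped independently with probability q = d/6.8, where d is the mean reduction. The new count is binomial given the old one. Patients below 5 are removed, and the mean is taken over the rest.

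| Model | True early reduction | Arm removed | Visible among remaining | Hidden |
|---|---|---|---|---|
| A | 0.10 | 2.7% (about 50) | 0.024 | 76% |
| A | 0.20 | 5.4% (about 100) | 0.050 | 75% |
| B | 0.10 | 2.0% (about 37) | 0.044 | 56% |
| B | 0.20 | 4.1% (about 75) | 0.087 | about 57% |

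In drugs per patient, the hidden part is 0.056 to 0.076 for a reduction of 0.10, and 0.113 to 0.150 for 0.20. Against the planned 0.70 this is 8% (0.056/0.70) to 21% (0.150/0.70).

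**Step 4: does this carry into the planned model?** Step 3 compares mean counts at the check. Section 7.5 adjusts for baseline medication use and estimates change through an intervention-by-time interaction. If the baseline count is taken at the rolling date, a drug stopped earlier is already in the baseline value of every patient who remains. Fixing the eligibility list alone would therefore not bring that early reduction back; the baseline count must be taken on the same fixed date.

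**The case against.** The strongest reply is that the single list is the more natural reading. The sentence in 3.1 names only the diagnoses and an appointment booked ahead. It does not mention the medication count, and it can be taken as shorthand for the weekly appointment search in 2.2. The timeline and the schedule in 4.1 agree. A reader might infer that the protocol recomputes medication count, diagnosis and PCP clinic every week. The documents do not say so; that is one reading and not a stated rule. The contradiction stands all the same, because 2.1 and 4.2 attach the criterion and the exclusions to a baseline that is plainly rolling.

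A second reply is that controls are screened by identical methods. This equalises the procedure, but only one arm's clinicians are educated, so the same filter can select differently in the two arms.

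A third reply concerns size. The amount of early deprescribing is assumed, with nothing in the protocol to anchor it. Section 7.2 expects about 80% of the eligible intervention population to be mailed, which limits the unmailed route. Model A also gives a patient on five drugs the same chance of losing one as a patient on ten, and so hides more than Model B. These points stand: the figures show direction and order of size only.

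Finally, setting the exclusions on one early date would alter a criterion that 2.1 applies at baseline. That is fair, and the fix treats the exclusions separately.

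**Conclusion.** The protocol is inconsistent on when eligibility is set, and nothing in it puts the eligibility date or clinic attribution before clinician education. If the rolling text is followed, a threshold on a primary outcome is applied after the clinician component has begun in one arm. For medication count the resulting bias is toward no effect under both models. Its size is unknown. Under the assumptions above, 2 to 5% of the intervention arm would be removed, and between over half and three quarters of the reduction made before the check would be hidden. Reductions made after entry are not affected by this mechanism.

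Two further inferences are tempting but not supported. One is that patients who change PCP would enter the other arm: the protocol is silent on the attribution date and does not say that attribution is re-read. The other is that the PIM outcome is biased in the same direction: the calculation covers counts only, and the PIM direction has not been shown.

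**What to change.** Reconcile sections 2 (timeline), 2.1, 2.2, 3.1, 4.1, 4.2 and 7.5, and state the following.

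- Eligibility for the primary analysis (age, diagnosis, comorbidity, five or more chronic medications) and PCP-clinic attribution are set once, from VDW data on one calendar date before the first clinician session, identically for all 18 clinics.
- The weekly step only searches that list for upcoming PCP appointments. Patients are analysed in the arm of their clinic on that date.
- The medication and PIM counts on that same date are the baseline values in the primary model.
- The time at which the long-term-care, hospice and home-rounding exclusions are applied is given explicitly, by the same rule in both arms.
- The sentence in 7.5 that admits members eligible at either baseline or follow-up is aligned with this. Members who become eligible later may form a secondary cohort.

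The cost is protocol wording and one saved extract. The planning count in 7.2 is itself a single-time roster ("members who would be eligible for the intervention in November 2018"), so the planned size should hold. There are two small downsides: newly eligible members leave the primary cohort, and patients with late visits have a longer interval from baseline to index visit.
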